### Statistical methods

We use SAS v9.3 software (SAS institute, Cary, NC, USA) for data analysis, and will not impute missing data. A significance level of 5% will be considered for the analysis.

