### Constitution of the cohort

The prospective cohort study will be conducted on a sub-sample of the participants (Fig. 1). The study biostatistician will arrange a cohort of 400 subjects selected through random sampling stratified by sex (male/female), age (determined by interquartile range of the collected data), investigating ED (1 to 6), and IES-R score (< 12, 12 to 34, > 34). Selected subjects will receive the questionnaires by email or postal mail and will be interviewed by telephone at 3 months (± 15 days) after the index trauma. Mental health professionals (a psychologist, psychiatrist, or resident in psychiatry) who have had special training on the PCL–5 application will conduct the interview.

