Additionally, through a telephone interview, a mental health professional (psychologist, psychiatrist, or psychiatric intern) will assess PTSD using the PCL–5 questionnaire and determine whether the subject received any therapeutic care in the 3-month period. The estimated duration of this interview is 15 to 30 min.

Inclusion, follow-up and data collection stages are presented in Table 1.

We will apply the following measures in order to limit the number of dropouts:

Selected patients will receive an email or a postal mail reminding them of their participation in the second stage of the study around 1 month prior to the theoretical date of the interview.

Within 15 days of the interview, we will contact the subject via telephone or email in order to set the date and time for the interview.

In case the first attempt to contact the subject is unsuccessful, we plan three more attempts of telephone call or email. If we fail to establish any (telephone/email) contact up to the intended date of the interview, the subject will be considered as lost to follow-up.

Subject participation in the study will end with the completion of this telephone interview.

Patients with an IES-R score of > 34 will be proposed to consult a specialized healthcare professional (psychiatrist or addictionologist) for the diagnosis and treatment (if necessary) of PTSD or its complications (alcoholism and/or substance abuse, suicidality, and depressive symptomatology).

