### Sample size

The total number of ED visits in the assigned six centers over a period of 1 month is more than 20,000. We plan to screen around 15,000 patients (75%) with an age range of 18 to 70. Following a traumatic context, 10 to 50% of survivors consult EDs [3, 15, 79, 80]. Considering the most conservative hypothesis (10% of the 15,000 visiting 18–70 year old patients), we estimate that 1500 patients could be included in the study to participate in the cross-sectional part of the study.

The main objective of the cohort study is to identify factors associated with the occurrence of 3-month PTSD. In the literature, incidence of PTSD in various populations and after different types of trauma usually ranges from 30 to 60% [3, 15, 79, 80]. Considering the hypothesis of a 40% incidence of PTSD in the “unexposed” group, the inclusion of 305 patients should allow, with an alpha risk of 0.05, and a power of 80%, to identify factors associated with a relative risk of at least 1.4 [81].

As we anticipate 30% of the subjects may be either lost to follow-up or unwilling to participate at 3 months, we will randomly select a cohort of 400 patients.

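### Imputation is ruled out although 30% of 3-month outcomes are expected to be missing, and no correction for non-response is stated, so cohort results are complete-case

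*Protocol article*

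**What the plan says.** The Statistical methods section gives one rule on missing data: the study "will not impute missing data". It is not limited to outcomes or to predictors.

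The Sample size section states that "we anticipate 30% of the subjects may be either lost to follow-up or unwilling to participate at 3 months", and that "we will randomly select a cohort of 400 patients". Three months is when the PCL-5, the primary endpoint of the cohort, is collected by telephone.

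The sections on primary and secondary outcome analysis plan univariate and multivariate logistic models, with at most twelve explanatory variables, and a 3-month proportion with PTSD with its 95% confidence interval. Neither mentions adjustment for non-response. The descriptive analysis section plans to compare those lost with those who completed, and included with non-included patients.

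On contact, Constitution of the cohort has subjects "interviewed by telephone at 3 months (± 15 days) after the index trauma". Data collection says that if no contact is made "up to the intended date of the interview, the subject will be considered as lost to follow-up".

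**The concern.** A ban on imputation with no stated alternative leaves complete-case analysis as the default. The incidence then describes responders, and it equals the cohort incidence only if responders and non-responders have the same PTSD rate. That is doubtful here: avoidance is among the symptoms of PTSD, and the interview is about the trauma.

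The models lose patients twice: once for a missing outcome, and again for any missing predictor. Predictors come from about 30 minutes of self-completed questionnaires in the ED and from patient files, so some gaps are likely.

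The protocol sees the threat. It names unwillingness to participate as a source of selection bias, faults earlier prospective work for high loss, and presents its cohort as representative of ED visitors. An undefined cut-off for contact could add avoidable losses.

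**Working it through.** **Inputs from the protocol article.** Cohort 400, loss 30%, analysable target 305, incidence 40% in the unexposed, relative risk 1.4, alpha 0.05, power 80% (Sample size); 122 events and a cap of twelve variables (Primary outcome criteria analysis). **Assumed, not in the article:** PTSD rates among those lost, response rates by group, and item-missingness rates.

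**The plan's own figures.** Comparing 40% with 0.40 × 1.4 = 56%, two-sided, 1:1 (assumed), pooled variance:

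n per group = [1.960 × √(2 × 0.48 × 0.52) + 0.842 × √(0.40 × 0.60 + 0.56 × 0.44)]² / 0.16² ≈ 152, so 304 in total, which agrees with 305. Events: 305 × 0.40 = 122. Cap: 122 / 12 ≈ 10 events per variable.

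**Responders at the stated loss.** 400 × 0.70 = 280, with 280 × 0.40 = 112 events. That 280 is below 305 is a separate sample-size matter and is not counted here.

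**Incidence.** True incidence = 0.70 × (rate in completers) + 0.30 × (rate in those lost), with 40% in completers:

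- 20% in those lost: 0.28 + 0.06 = 34%
- 60% in those lost: 0.28 + 0.18 = 46%
- Extreme bounds: 112/400 = 28% and (112 + 120)/400 = 58%

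For scale, the 95% half-width at n = 280, treated as a simple random sample, is 1.96 × √(0.40 × 0.60 / 280) ≈ 5.7 points. An error of 6 points is about as large, and the reported interval would not show it.

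In the other direction, with true incidence 40% and overall response 70%, complete-case incidence = 0.40 × r / 0.70, where r is the response rate among cases. It is 34.3% for r = 0.60 and 45.7% for r = 0.80.

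**Odds ratios.** True value: (0.56/0.44) / (0.40/0.60) = 1.91.

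- If response depends on PTSD alone, the response rates cancel and 1.91 is unchanged.
- If exposed cases respond at 60% and the other three cells at 70%: 1.91 × 0.60/0.70 = 1.64.
- If exposed cases respond at 50%: 1.91 × 0.50/0.70 = 1.36.

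**Missing predictors.** With all twelve variables used and each missing in a share m of patients, independent gaps leave 280 × (1 − m)^12. If all gaps fall in the same patients, 280 × (1 − m) remain. Events are 40% of each.

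| m (assumed) | Independent: patients / events | Events per variable | Fully clustered: patients / events |
|---|---|---|---|
| 2% | 220 / 88 | 7.3 | 274 / 110 |
| 3% | 194 / 78 | 6.5 | 272 / 109 |
| 5% | 151 / 61 | 5.0 | 266 / 106 |

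**Contact rule.** Data collection says that making contact is what fixes the date and time of the interview. A subject never reached therefore has no agreed date, and the intended date most naturally means the theoretical 3-month date. On that reading contact closes up to 15 days before the window in Constitution of the cohort ends. If the intended date may be any day in the window, there is no conflict. The article does not say which.

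**The case against.** A reader might infer that the plan forbids any handling of missing data. It does not: only imputation is excluded. Weighting and sensitivity analyses remain open, and an analysis plan that is not shown may specify them. This stands, and their absence from the article alone would be no finding. What remains open to challenge is the explicit exclusion of imputation, which a later analysis plan could not reverse without contradicting the protocol.

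A reader might also infer that the predictor results are biased. That is not shown. Odds ratios survive when response depends on the outcome alone, and conditional odds ratios survive when it depends only on covariates in the model. Since predictors are the cohort's primary objective and incidence is secondary, this limits the point.

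It is tempting to set 194 patients and 78 events against the planned 305 and 122. That would mix in the drop to 280, which occurs under any missing-data rule. The 194 is itself an upper-end loss: twelve is a maximum, sex and age come from the file, a trained interviewer collects baseline data, and gaps tend to cluster.

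Finally, a reader might conclude that half the interview window is discarded. That holds only if the intended date is the 3-month date, and the term is undefined.

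The retention measures (reminder, scheduling contact, three further attempts, pre-paid envelope) are sensible, but the 30% is the loss the protocol itself plans for.

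**Conclusion.** The point holds in limited form. Imputation is excluded, 30% of primary outcomes are expected to be missing, and no correction is stated, so the 3-month incidence and the models are complete-case as written. Incidence is the more exposed: an error of up to 6 points either way if PTSD among those lost is 20% to 60%, an assumed range. Bias in the odds ratios is possible and conditional on joint dependence of response on factor and PTSD.

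Listwise deletion could also take events per variable from about 9 among 280 responders (112/12) to about 6.5, against the roughly 10 behind the twelve-variable cap. This assumes twelve predictors and 3% independent missingness; clustered gaps would cost far less.

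This is an inexpensive improvement to a stated rule and does not invalidate the design. The contact rule is an ambiguity to be resolved.

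**What to change.** Replace the no-imputation sentence with two provisions:

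1. Weight responders by the inverse of their estimated probability of response, modelled on baseline IES-R, PDEQ, STAI-Y, QIDS-SR16, AUDIT, SSQ6, sex, age and ED, and multiply by the sampling weight. Use these weights for the 3-month incidence and as a sensitivity analysis for the logistic models.
2. Multiply impute missing baseline predictors, with the 3-month outcome in the imputation model, and report the complete-case models as a sensitivity analysis.

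Reconcile Constitution of the cohort with Data collection: define the intended interview date against the ±15-day window, so that no subject is counted as lost while an interview would still fall inside it.

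The baseline data are already collected, so the analysis cost is programming. Weighting costs some precision and recovers no lost outcomes. Both provisions need a missing-at-random assumption, which must be defended; complete-case incidence needs the stronger one that responders represent everyone. The contact change may mean spreading attempts over a longer period.

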#### Descriptive analysis of the emergency departments and patients participating in the study

Unwillingness of the EDs and/or patients to participate in the study could lead to selection bias. For a critical appraisal of the study findings, we will compare the characteristics of patients included and not included in the cross-sectional study and/or in the cohort study.

Mean and standard deviation (with 95% confidence interval of the mean) will summarize continuous normally distributed variables. Median and interquartile range will summarize continuous non-normally distributed variables. Frequency tables will summarize discrete variables.

There will be a description of characteristics of the two populations studied: total population included in the first cross-sectional phase and the prospective cohort population followed-up at 3 months. Additionally, we will describe and compare characteristics of the subjects who were lost to follow-up to those who completed the follow-up.

#### Primary outcome criteria analysis

To assess the baseline risk of developing PTSD based on the IES-R score (< 12, 12 to 34, > 34) we will calculate the proportion of the subjects at high risk (IES-R score > 34) and moderate-risk (IES-R score 12 to 34) to develop PTSD and their 95% confidence interval.

To analyze the biopsychosocial factors associated with the occurrence of PTSD at 3 months (yes / no) we will employ a univariate model. For statistical testing, we will use the Chi-squared test for qualitative variables, Student’s test for quantitative variables following a normal distribution, Wilcoxon test for quantitative variables following a non-normal distribution, and a Kruskal & Wallis rank test for ordered quantitative variables of the score type. Univariate and multivariate logistic regression modeling will facilitate estimation of the association between the studied factors and the 3-month risk of PTSD by calculating the crude and adjusted odds ratio and their 95% confidence interval.

Among 305 analyzable patients, with a 40% incidence rate of PTSD, we expect 122 patients in the PTSD group. To ensure the convergence and robustness of the statistical model, we will not integrate more than twelve explanatory variables into the multivariate predictive model [82].

#### Secondary outcome criteria analysis

In the cross-sectional study subjects, we will analyze the proportion of patients at moderate risk (IES-R score 12 to 34) and at high risk (IES-R score > 34) of PTSD at inclusion and their 95% confidence interval.

In the cohort study population, we will analyze the proportion of subjects with a diagnosis of PTSD at 3 months with its 95% confidence interval.

To describe results of the questionnaires, we will consider total score of PDEQ, STAI-Y (A & B forms), AUDIT, Fagerström, QIDS-SR16 and SSQ6 evaluated at inclusion. To present the results of the questionnaires at 3 months, we will focus on total score of STAI-Y (A & B forms), AUDIT, Fagerström, QIDS-SR16 and SSQ6 evaluated again after 3 months.

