## Methods/design

This multicenter study will be conducted in two stages. The first stage will consist of a cross-sectional study within all consecutive patients admitted to the participating EDs following a recent trauma (< 1 month), to systematically measure their risk of PTSD. The second stage will be a prospective cohort study designed to analyze the relationship between PTSD occurrence and its putative predictive factors in a sub-sample of patients randomly selected among those identified as “at moderate or high risk” for developing PTSD at admission to the ED and followed-up for 3 months.

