### Data collection

Table 1 summarizes the different stages of data collection.

**Table 1 Tab1:** Patient inclusion, follow-up, and data collection stages of the study

Steps	Preselection	V1 Inclusion	Establishment of the Cohort	V2 Telephone Follow-up End of the Study
Preselection Criteria Verification *(1)*	X			
Information, Consent Collection and Inclusion		X		
Self-administered questionnaires {IES–R; PDEQ; STAI-Y (A & B forms); AUDIT; Fagerström; QIDS-SR16; SSQ6}		X		
Clinical Data Collection & Self-administered questionnaire (risk factors) *(2)*		X		
Stratified sampling (weighted)			X	
Mailing self-administered questionnaires to subjects to prepare for the telephone interview			X	
Telephone Interview: PCL–5; STAI-Y (A & B forms); AUDIT; Fagerström; QIDS-SR16; SSQ6 (+ back to work time)				X
Intercurrent psychological care (consultation, hospitalization, psychotropic)		X		X

(1) Emergency patient with a recent history of trauma (< 1 month), aged 18 to 70 years, speaks French, and has no guardianship

(2) This self-administered questionnaire consists of PTSD risk factors

Following preselection and written informed consent, patients will be identified as study subjects. At the inclusion phase, he/she will receive self-administered questionnaires to measure acute stress (IES–R), dissociative experiences (PDEQ), anxiety disorder (STAI-Y; A & B forms), social support (SSQ6), alcohol and/or tobacco addiction (AUDIT & Fagerström test), depressive symptoms and suicidality (QIDS-SR16), marital stability, family history of mental health problems and/or instability, socio-economic and familial status, history of trauma exposure, and past psychiatric history. Demographic and physical health-related data will be collected from his/her medical file.

At 3 months after the index date, the cohort study participants will receive self-administered questionnaires by an email {a link with access code to an ePRO (electronic patient reported outcomes) for online completion of questionnaires} or by postal mail (attached with a pre-paid return envelope). The online version of the questionnaires will have to be completed at least one day prior to the telephone interview. These questionnaires will help us assess trauma impact on the patient’s occupational and psychosocial functioning {SSQ6 & STAI-Y (A & B forms)} and PTSD complications and comorbidities such as depression & suicidality (QIDS-SR16), and addiction (AUDIT & Fagerström test).

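### The cohort is drawn by a stratified sample labelled weighted, but the planned 3-month incidence and models do not use the design; the overall incidence is biased if sampling fractions differ by IES-R class

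*Protocol article*

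**What the plan says.** Under *Constitution of the cohort*, the protocol article plans a "cohort of 400 subjects selected through random sampling stratified by sex (male/female), age (determined by interquartile range of the collected data"), with investigating ED (six) and IES-R class (three, including a class below 12) as further strata. Table 1 under *Data collection* lists this step as "Stratified sampling (weighted"). No section gives sampling fractions, states the allocation or explains the word weighted.

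Under *Secondary outcome criteria analysis*, the 3-month incidence is described as follows: "In the cohort study population", "we will analyze the proportion of subjects with a diagnosis of PTSD at 3 months with its 95% confidence interval". Under *Primary outcome criteria analysis*, the factors are examined with chi-squared, Student, Wilcoxon and Kruskal-Wallis tests, and "Univariate and multivariate logistic regression modeling will facilitate estimation of the association" through crude and adjusted odds ratios, with at most twelve explanatory variables. Weights, stratum terms and design-based variance are not mentioned. Table 2 (*PTSD risk factors*) lists sex and age, but neither IES-R nor ED.

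The source population is described in two ways. *Primary objectives* and the opening of *Methods/design* take the cohort only from moderate- and high-risk patients ("randomly selected among those identified as “at moderate or high risk” for developing PTSD at admission to the ED"), while *Constitution of the cohort* keeps the class below 12. The abstract's discussion calls the cohort representative of ED visitors.

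**The concern.** IES-R class is not a neutral stratifier. *Primary outcome criteria* defines its three classes as low, moderate and high risk of PTSD, and the *Background* treats acute stress as a strong predictor of PTSD. If one class is sampled more heavily than another, a raw proportion moves towards the risk of the over-sampled class and no longer describes the patients enrolled in the cross-sectional step. The 3-month incidence is a stated secondary objective, so this would affect a reported result. Standard errors that ignore the strata would also be wrong, in one direction or the other. For the models, the question is whether the variables that governed selection are in the regression.

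**Working it through.** **The plan's own figure.** *Sample size* gives 305 analysable patients for 40% against 40% × 1.4 = 56%, alpha 0.05, power 80%. With two-sided alpha, equal groups and no continuity correction, n per group = [1.960 × √(2 × 0.48 × 0.52) + 0.842 × √(0.40 × 0.60 + 0.56 × 0.44)]² / 0.16² = 151.9. That rounds up to 152, or 304 in total. The figure therefore reproduces as a simple-random-sample calculation with no design effect.

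**Inputs for the incidence.** n = 305 is from the article. The class shares W, PTSD risks r and allocations a (each in the order low, moderate, high) are all assumptions, because the article gives none of them.

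**Formulas.** Population incidence P = Σ W r. Expected unweighted estimate U = Σ a r. Bias = U − P. Simple SE = √[U(1 − U)/n]. Weighted stratified SE = √[Σ W² r(1 − r)/(n a)]. Kish factor = Σ W²/a.

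**Central illustration**, W = 40/35/25% and r = 5/20/50%, so P = 0.020 + 0.070 + 0.125 = 21.5%:

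| Allocation | Unweighted (simple 95% CI) | Weighted (stratified 95% CI) | Bias, points | Coverage of simple CI | Kish |
|---|---|---|---|---|---|
| Proportional | 21.5% (16.9–26.1) | 21.5% (17.3–25.7) | 0 | about 97% | 1.00 |
| Equal | 25.0% (20.1–29.9) | 21.5% (17.5–25.5) | +3.5 | about 73% | 1.04 |
| 20/40/40 | 29.0% (23.9–34.1) | 21.5% (17.5–25.5) | +7.5 | about 16% | 1.26 |

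**Range under equal allocation**, changing both mix and risks:
- Mix 40/35/25, risks 5/20/40: 19.0% against 21.7%, +2.7 points.
- Mix 50/30/20, risks 5/20/50: 18.5% against 25.0%, +6.5 points.
- Mix 60/25/15, risks 5/25/60: 18.25% against 30.0%, +11.75 points.

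This is the +3 to +12 quoted. A frame closer to even thirds gives less: mix 30/40/30 with risks 5/20/50 gives +0.5. The largest value tried is +15 (mix 50/30/20, risks 10/40/70, allocation 20/40/40: 31.0% against 46.0%, Kish 1.58, effective n about 194). If only moderate- and high-risk patients are sampled, in equal numbers, the three mixes above give +1.7, +3.0 and +4.4 points.

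**Sparse cells.** Reading the age rule as quartiles (an assumption), there are 2 × 4 × 6 × 3 = 144 cells, so 400/144 = 2.8 draws per cell; without the class below 12 there are 96 cells, or 4.2. I simulated proportional allocation of 400 from 1500, rounded cell by cell, with assumed ED shares of 10 to 25%. Mean bias was 0.1 points (95% of draws −0.2 to +0.4) for the 50/30/20 mix and 0.3 points (−0.2 to +0.7) for the 60/25/15 mix. Rounding alone is unimportant.

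**Odds ratios.** Assume a factor present in 30/45/60% of the low/moderate/high classes, baseline risks 5/20/50% and a conditional odds ratio of 1.0. The crude odds ratio is 1.64 under proportional, 1.62 under equal and 1.47 under 20/40/40 allocation. Nearly all of the distance from 1.0 is confounding by IES-R, present under any allocation; the sampling design moves it little.

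**The case against.** The strongest reply is that the article never says any IES-R class is over-sampled. Weighted may mean proportional to stratum size; the claim that the cohort is representative fits that reading. The sample is then self-weighting, as the first row of the table shows. This stands, and it makes the bias conditional.

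A reader might infer from the 144 cells that equal selection probabilities are impossible and bias therefore certain. The documents do not support that: rounding bias is a fraction of a point. A reader might also infer that the logistic results are invalid. That goes too far as well: selection depends on baseline covariates, not on the outcome, so a correctly specified unweighted model containing the stratifiers estimates the adjusted odds ratios consistently, and sex and age are already candidates.

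There is also mitigation. Secondary results are to be shown by IES-R risk level, and within a level the IES-R fraction cannot bias the proportion. The incidence is stated for the cohort, not for all enrolled patients. Finally, a condensed article may leave weights to a fuller document.

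What remains is that the article does set out its analysis in detail, names only unweighted methods, omits two stratifiers from its candidate list, and also presents results for the total population, where the by-level tables do not help.

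**Conclusion.** The concern holds conditionally. The planned analysis as written does not use a sampling design that stratifies on an expected strong predictor of the outcome. If fractions differ by IES-R class, the unweighted overall incidence is biased, by about +3 to +12 points under equal allocation with the assumed mixes and risks; the sign would reverse if low-risk patients were over-sampled. These assumed incidences (about 18 to 19%) are well below the article's planning figure of 40%, so the sizes are illustrations, not predictions. If allocation is proportional, the estimate is unbiased and the simple interval is only slightly too wide (16.9–26.1% against 17.3–25.7%). Adjusted odds ratios are at risk only where stratifiers are omitted, and the design effect on crude odds ratios is small in the worked example. The point is worth settling before the draw, but it is not an established error; my confidence is moderate because the allocation is unstated.

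**What to change.** 1. Fix the sampling fraction for each stratum, record it before the draw, and say what weighted means.
2. Estimate the overall incidence and its interval with inverse-fraction weights and a stratified variance, for example with SURVEYFREQ in the SAS software already named. This is at least as good under either reading: a slightly narrower valid interval if allocation is proportional, and removal of the bias if it is not.
3. Include IES-R class and ED, with sex and age, in the multivariable model within the twelve-variable cap.
4. Collapse sparse strata, for example to IES-R class by ED (3 × 6 = 18 cells, about 22 draws each).
5. Reconcile *Primary objectives* and *Methods/design* with *Constitution of the cohort* on whether patients with IES-R below 12 are sampled, so that the population behind the incidence is clear.

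The cost is analysis wording and code. Intervals may be somewhat wider if weights vary strongly, although in the table above the weighted interval is not wider than the simple one. The stratifiers take four of the twelve variables. ED as a fixed effect costs 5 parameters; with IES-R class (2), sex (1) and age (1 if linear, 3 if quartiles) the total is 9 to 11, against the 122 events the article expects. Adjusting for IES-R also makes the other odds ratios conditional on acute stress. Where that is not wanted, a weighted logistic model (SURVEYLOGISTIC) without IES-R is the alternative; using weights and forcing in every stratifier is largely redundant.
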